### Case Selection Criteria

Scribes will select cases based on a rubric designed to capture diagnostic uncertainty. If a case meets any of the following criteria, it will be entered into the Human Dx platform: (1) a new symptom or abnormality in laboratory, physical exam, or radiographic finding; (2) a recurrent symptom or abnormality in laboratory, physical exam, or radiographic finding without a clear diagnosis or etiology; (3) a pending diagnostic test ordered to evaluate a new or unresolved condition; (4) empiric treatment provided without complete diagnostic certainty; and (5) if the clinician submitted a request for electronic consultation from a specialist within the health network for a diagnostic or management problem. Clinicians may also flag a case for review that the scribes will enter into the Human Dx platform whether or not it meets the above rubric’s selection criteria.

### Data Collection and Study Procedures

#### Study Period

We will follow participants’ consecutive clinic sessions over a period of 4 to 8 weeks to select a minimum of 20 cases per clinician. After all postvisit questionnaires are completed, the participant will participate in a 1-hour exit interview including an in-person survey and semistructured interview to assess the efficacy and usability of collective intelligence for medical diagnosis from the perspective of primary care and urgent care clinicians (Figure 3).

**Figure 3 figure3:**
[figure not shown]
Study procedures. At baseline, clinicians are recruited and cases are collected and randomized to the intervention and control groups. Post-visit questionnaires will assess diagnostic confidence (the primary outcome) for each case. Exit interview sessions at 8 weeks will explore clinicians’ perception on usability. At 6-9 months, will conduct electronic medical record review to adjudicate clinic outcomes (secondary and exploratory outcomes).

#### Postvisit Questionnaires

For cases randomized to the control group, a research assistant will email the study participant a brief one-line description of the case accompanied with instructions to fill an online postvisit questionnaire (Multimedia Appendix 1) that captures the participant’s clinical thinking. The brief one-line description is important to alert the participant to which case the questionnaire is referring; we will keep each one-line description in the study’s records to act as a case identifier. For cases randomized to the intervention, the participants will receive instructions to complete an online questionnaire in similar fashion as described above for the control cases. In addition, we will provide the participant a Web link to access the collective intelligence output for the intervention case as well as the questionnaire that will assess the impact of the collective intelligence on their clinical thinking (eg, confidence and decision making; see Multimedia Appendix 1). All instructions to participants will be sent as a single email. Participants will be instructed in the email to review the collective intelligence output for intervention cases only when prompted, to ensure that they respond to survey questions designed to assess their initial clinical thinking (for both intervention and control cases) before reviewing the collective intelligence output that will be available only for intervention cases.

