Once the collective intelligence output becomes available for a case, the study team randomizes it to the intervention or control cases. The study team assigned each case a unique study identification number for tracking purposes. Using a random number generator in blocks of four, we will randomize half of the cases, for each clinician, to an intervention group in which the clinician will receive a collective intelligence output between 60 and 80 hours from the time the clinician saw the patient in the clinic (ie, within 24-36 hours of case entry). For cases randomized to the controlled group, Human Dx will generate collective intelligence, but it will not be shared with the clinician. Clinicians will complete an online postvisit questionnaire for all of their cases (control and intervention) that provides their initial impressions of the case (eg, differential diagnosis and perceived case difficulty) and level of diagnostic confidence. The questionnaire for cases assigned to the intervention group includes additional questions that the clinician will answer after reviewing the collective intelligence output to assess the effect of the output on their diagnosis, plan, and confidence. The study scribes and the *contributors* on Human Dx will be blinded to case randomization.

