#### Exploratory Analyses

We will perform mixed-effect multivariable logistic regressions to compare diagnostic confidence, T2Dx, and diagnostic accuracy of intervention versus control cases, accounting for clustering by clinician and adjusted for baseline diagnostic uncertainty, perceived case difficulty, patient age, race, gender, number of comorbid conditions, type of visit (new, returning, drop-in, or urgent care), and primary care clinician characteristics such as professional degree (NP vs MD), specialty (family vs internal medicine), and years of experience. We have chosen covariates a-priori based on clinical judgment. For cases randomized to the intervention, mixed-effect bivariate logistic regressions will compare physicians’ diagnostic accuracy before and after reviewing the collective intelligence, adjusted for the aforementioned clinician characteristics. We will use bivariate and multivariable linear regressions to compare the number of diagnostic testing and use logistic regressions to compare the occurrence of unexpected clinical visits at 30 days between intervention versus control cases.

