#### Handling of Missing Data

Our general approach to missing data will be multiple imputation. It is possible that our primary outcome of diagnostic confidence will have a level of missing data, as it will depend on the response rate to survey questions. In addition to multiple imputation under the standard assumption that data are missing at random, given the covariates and outcomes that are observed, we will also implement sensitivity analyses using imputation under plausible missing-not-at-random scenarios. To maximize survey completion rates and thereby minimize the level of missing data, we will send 3 email reminders at 3 days, 7 days, and 14 days if the initial survey request was not completed. We will leave hard copies of the survey in clinicians’ mailboxes if the participants have not completed the online survey after the 3 email reminders.

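### The answers meant to precede the collective intelligence output are protected only by an email instruction and are given with allocation visible, which weakens the exploratory before-after and adjusted analyses

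*Protocol article*

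**What the plan says.** All of this is in the protocol article.

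- **Order of events.** Under Selection, Entry, and Randomization of Clinical Cases: "Once the collective intelligence output becomes available for a case, the study team randomizes it to the intervention or control cases". The questionnaire goes out afterwards, so every answer on it is given after randomization.
- **What control cases receive.** Under Postvisit Questionnaires, "a research assistant will email the study participant a brief one-line description of the case accompanied with instructions to fill an online postvisit questionnaire".
- **What intervention cases receive.** The same, and then: "In addition, we will provide the participant a Web link to access the collective intelligence output for the intervention case".
- **How it is sent.** "All instructions to participants will be sent as a single email".
- **The safeguard.** "Participants will be instructed in the email to review the collective intelligence output for intervention cases only when prompted". The stated purpose is that initial thinking is recorded first.
- **Who is blinded.** "The study scribes and the *contributors* on Human Dx will be blinded to case randomization". Participating clinicians are not listed.
- **Paper fallback.** Under Handling of Missing Data, after reminders at 3, 7 and 14 days: "We will leave hard copies of the survey in clinicians’ mailboxes if the participants have not completed the online survey".
- **Use of the initial answers.** Under Exploratory Analyses, models within the intervention cases will "compare physicians’ diagnostic accuracy before and after reviewing the collective intelligence". The adjusted between-arm models for confidence, time to diagnosis and accuracy include baseline diagnostic uncertainty and perceived case difficulty as covariates.

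**The concern.** The plan treats the order of answering as necessary but relies on the clinician's compliance to secure it. The output concerns a real patient without a confirmed diagnosis, so a clinician has a practical reason to read it at once and complete the form later. With reminders running to 14 days, a late responder may have held the link for two weeks before recording initial impressions. A paper form cannot enforce any order.

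Two problems follow. First, an initial differential, difficulty rating or confidence rating given after the output was opened already contains the intervention. This can occur in one arm only. Second, the presence or absence of a link tells the clinician the allocation before the initial items are answered, even if the link is left unopened. Clinicians must learn the allocation eventually, but not before those items.

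At stake are a before value that may not be one, and adjustment for covariates that treatment or knowledge of allocation may have changed.

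**Working it through.** The plan states no figure on this point, so there is none to reproduce. The check traces which analyses use the initial answers and then shows the form of the bias.

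**Step 1: which analyses are exposed.**

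| Analysis | Uses initial answers? | Exposed? |
|---|---|---|
| Primary: confidence by arm, bivariate logistic model | No for intervention cases: the rating is taken after the output | No |
| Secondary: time to diagnosis, Cox model with intervention status as primary predictor | No: ascertained from the chart | No |
| Exploratory: accuracy before and after, intervention cases | Yes, as the before value | Yes |
| Exploratory: adjusted between-arm models | Yes for perceived difficulty; for baseline uncertainty only if it comes from the questionnaire | Yes |

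**Step 2: before-after accuracy.** Let D be the true change in accuracy and p the share of intervention cases in which the output is opened first. Assume that an early-opened case shows no further change and that D is the same in early-opened and other cases. Then

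measured change = (1-p) x D + p x 0 = (1-p) x D.

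The documents give neither p nor D. The planned number of intervention cases is 33 clinicians x 10 = 330. For assumed values of p:

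- p = 0.10 (33 cases): 0.90 of D remains
- p = 0.25 (about 83 cases): 0.75 of D remains
- p = 0.50 (165 cases): 0.50 of D remains

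**Step 3: adjusted between-arm effect.** Let d be the true effect on the outcome, s the shift that seeing the output causes in the covariate, and b the slope of outcome on covariate. Early opening creates an arm difference of p x s in the covariate. On a linear approximation,

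adjusted effect = d - b x p x s.

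For initial confidence, s and b are both positive if the output raises confidence. For perceived difficulty, both are negative if the output makes a case look easier and easier cases are rated with more confidence. Either way b x s is positive and the adjusted effect moves towards zero.

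In the special case where the covariate is on the outcome's scale and s = d, the factor is 1 - b x p. With b assumed between 0.3 and 0.7:

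- p = 0.10: 1 - 0.07 = 0.93 to 1 - 0.03 = 0.97
- p = 0.25: 1 - 0.175 = 0.825 to 1 - 0.075 = 0.925
- p = 0.50: 1 - 0.35 = 0.65 to 1 - 0.15 = 0.85

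For a given p, the loss here is smaller than in the before-after comparison.

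**Step 4: knowledge of allocation.** A clinician who sees that an output is available might rate initial confidence lower, to leave room for it, or higher. Nothing in the documents fixes the sign or size.

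**The case against.** The strongest reply is that the main results do not depend on this. That stands: the primary comparison uses the post-output rating in intervention cases, time to diagnosis comes from chart review, and the exposed analyses are labelled exploratory and hypothesis generating. A reader might infer that the trial's primary result is compromised; the documents do not support that.

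Second, a reader might take it as established that the link is open and early viewing untraceable. The article does not say so. The questionnaire itself (Multimedia Appendix 1) is not shown, and a lock or access log may exist. What can be said is that none is stated, and that an instruction to wait is needed only if the link can be opened sooner.

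Third, the source of baseline diagnostic uncertainty is not given. It could be the initial confidence item or something drawn from the scribes' case-selection rubric, which is applied before randomization. Only perceived case difficulty is clearly tied to the questionnaire.

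Fourth, it is tempting to express the loss in percentage points using the 20% difference in the sample size section. That figure is a between-arm difference in confidence, whereas the planned before-after comparison is of accuracy, so it does not transfer.

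Fifth, early opening by itself pulls towards no effect and would not create a false benefit. This is correct, but it does not cover the effect of knowing the allocation.

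Finally, the article does not say whether the paper copies contain the post-output items or how many are expected.

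**Conclusion.** The point holds for the exploratory analyses only. The stated procedure gives no assurance that the initial answers precede the output, and it reveals the allocation before they are given. Early opening can contaminate only intervention cases. It would shrink the before-after accuracy change by the factor (1-p) and pull the adjusted between-arm effects towards zero by a smaller proportion under the assumptions shown. The bias from knowing the allocation has no predictable direction. The actual size cannot be computed, because the document gives no rate of early opening, no expected change in accuracy and no covariate slope.

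The conclusion assumes that no technical lock exists beyond what the article states, and that at least perceived case difficulty is taken from the postvisit questionnaire. It is worth correcting, but it does not threaten the unadjusted primary or the time-to-diagnosis analysis.

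**What to change.** **If cases are still being collected.** Send an identical email in both arms, containing only the case description and the questionnaire link. Put the output link inside the online questionnaire so that it appears, for intervention cases, only after the initial page has been submitted, locked and time-stamped. Flag paper completions. The cost is branching logic in the existing questionnaire and a revised email template.

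**If collection is complete.** The Abstract and Results report completion as of June 2019, although the Results also describe enrolment as active. In that case, compare link-open times with questionnaire times where such records exist and report the share opened early. Repeat the exploratory analyses without early-opened and paper cases, and repeat the adjusted models without covariates collected after randomization. This costs only analysis time. If no access records exist, say so and present the before-after accuracy result as possibly attenuated.

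In either case, state where baseline diagnostic uncertainty comes from and whether it is measured before randomization.

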#### Exit Survey and Interview

We will conduct an exit session to complete an in-person exit survey and semistructured interview with at least 6 participants from each health system (UCSF and SFDPH) for a minimum total of 12 and continue interviewing more participants (if needed) until we reach thematic saturation. Previous studies have suggested a small sample (*N*=10) can collect most of the salient ideas from semistructured interviews with basic elements for meta-themes emerging after just 6 interviews [15,16]. After we reach thematic saturation, we will stop conducting in-person interviews, but we will email Web links to the online exit survey to all remaining participants not invited for in-person interviews. The first part of the exit survey will collect data on clinician factors such as professional degree (MD vs nurse practitioner [NP]), years of practice, and medical specialty (family medicine vs internal medicine). We used a modified Technology Acceptance Model (TAM) framework to inform construction of the semistructured interview guide and the second part of the survey. TAM is a validated theory of technology acceptance that has been widely used outside of health care and has become an important theoretical tool for health IT research [17]. As a theory, TAM suggests perceived usefulness (PU) and perceived ease-of-use (PEU) as the 2 major factors that influence how users come to accept and use a technology. Our survey will also measure participants’ willingness or intention to use the collective intelligence platform beyond this study period—the interview guide will explore perceived barriers and facilitators that could influence their willingness to use. In addition to these concepts, our interview guide also includes additional constructs such as general satisfaction, trust, and system facilitators as well as supplemental open-ended questions to allow free expression of ideas. We will also ask participants to provide suggestions about the visual and content display of the platform output (see Multimedia Appendices 2 and 3 for contents of the exit survey and interview guide).

### Outcomes and Measurements

#### Primary and Secondary Outcomes

Our primary outcome will be self-reported diagnostic confidence as measured by response to the survey question in the postvisit questionnaire that asks participants after reviewing the collective intelligence output for cases randomized to the intervention group: “How confident do you feel about your diagnosis for this patient?” (Not at all, somewhat, moderately, and very). We chose this outcome based on previous literature in diagnostic safety suggesting that diagnostic confidence plays an important role in medical management, evolves over time in the process of making a diagnosis, and the ability to move diagnostic confidence may contribute to avoiding diagnostic error [18,19]. Furthermore, our preliminary studies for the proposed trial suggested that clinicians’ confidence in their clinical assessment is an important factor in their cognitive process for decision making and future approach to similar cases. We also chose this measure because it is likely the most sensitive to the impact of the collective intelligence on clinicians’ complex diagnostic decision-making process, whereas clinical outcomes such as *time to diagnosis* and diagnostic accuracy can be confounded by external health care system factors such as time to receive test results, financial incentives for diagnostic testing, and other factors. The secondary outcome will be *time to diagnosis*, defined as the interval between the time of the clinic visit from which a case with diagnostic uncertainty was identified for entry into the collective intelligence platform and the time at which the clinician will have established a diagnosis for that symptom or sign. We will ascertain the time of established diagnosis as the time at which the clinician documents the new diagnosis, the result for a confirmatory diagnostic testing becomes available, or empiric treatment was initiated. We will choose the earliest occurrence of any of these three events as the time of established diagnosis.

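### As described, primary confidence is a post-output re-rating in intervention cases and a single initial rating in control cases, so the contrast measures the output together with reconsideration and repeat questioning.

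*Protocol article*

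**What the plan says.** - **Primary outcome (Primary and Secondary Outcomes).** Self-reported confidence on a four-level item. For intervention cases the question is one that "asks participants after reviewing the collective intelligence output for cases randomized to the intervention group". The timing of the control rating is not given separately.
- **All cases (Selection, Entry, and Randomization of Clinical Cases).** Clinicians complete a questionnaire "that provides their initial impressions of the case (eg, differential diagnosis and perceived case difficulty) and level of diagnostic confidence".
- **Intervention cases only (same section).** The form "includes additional questions that the clinician will answer after reviewing the collective intelligence output to assess the effect of the output" on diagnosis, plan and confidence.
- **Order (Postvisit Questionnaires).** Clinicians are told to answer the items on initial thinking "before reviewing the collective intelligence output that will be available only for intervention cases". For control cases, a research assistant will "email the study participant a brief one-line description of the case accompanied with instructions to fill an online postvisit questionnaire"; nothing further is described for them.
- **Delivery (same section).** "All instructions to participants will be sent as a single email". For intervention cases the link to the output is provided as well, with an instruction to open it only when prompted.
- **Analysis.** The primary model is a bivariate logistic regression on intervention status, clustered on clinician. The exploratory models are "adjusted for baseline diagnostic uncertainty, perceived case difficulty" and other covariates. A further exploratory analysis compares accuracy before and after the output within intervention cases.
- **Objective (Abstract).** To assess the efficacy of a collective intelligence output.

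**The concern.** The two arms do not appear to be measured at the same point. In an intervention case the clinician records initial thinking, returns to the case with the output, and rates confidence again. In a control case the only described rating accompanies the initial impressions. Thinking about a case again, and being asked about it again, can move a self-rating whatever the output contains. The article itself says that confidence evolves during the diagnostic process, and the rating is an unblinded self-report. A difference between arms could therefore be credited to the output when part of it comes from the extra step. A larger sample would not remove that part.

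A second issue concerns the initial answers. Cases are randomized before the questionnaire goes out, and in intervention cases the output link is already in the clinician's inbox. Initial confidence, initial differential and perceived difficulty are thus post-randomization measurements in that arm, and only an instruction protects them. The exploratory before-after comparison and the adjusted models use such answers.

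**Working it through.** **1. Measurement sequence as described**

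| Step | Intervention case | Control case |
|---|---|---|
| Initial impressions recorded | yes | yes |
| Output reviewed | yes | no |
| Confidence rated after a further review of the case | yes, and this is the primary outcome | none described |
| Rating available for the primary analysis | post-output rating | rating given with initial impressions |

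The Abstract words the order differently: intervention clinicians complete the questionnaire after reviewing the output. On that reading too, only intervention clinicians review the case further before the rating that counts, so the asymmetry remains.

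**2. The plan's own sample size**

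Inputs from Sample Size Justification: 80% power, a 20% difference, r = 0.3, 33 clinicians with 10 + 10 cases (660 in total, 330 per arm). The control rate and alpha are not stated; I assume two-sided 5%.

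Design effect with 10 cases per clinician per arm: 1 + (10 − 1) × 0.3 = 3.7.

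For 55% versus 75%, without continuity correction:

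n = [1.96 × √(2 × 0.65 × 0.35) + 0.842 × √(0.55 × 0.45 + 0.75 × 0.25)]² / 0.20² = 88.1, rounded up to 89 per arm.

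89 × 3.7 × 2 = 659 cases, or 32.9 clinicians at 20 cases each. The planned 660 is therefore reachable, but only under an assumed control rate: over control rates from 10% to 70% the same formula gives 459 to 718 cases.

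**3. What a re-rating shift alone could do (illustration)**

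Assumptions, none of them given in the article: the output has no effect; the extra step raises the share rated confident by s points from 50%; confidence is cut into two classes, as in the sample-size statement; two-sided 5% test.

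Let f be the variance factor and p̄ the mean of the two proportions p1 and p2.

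- SE0 = √(f × 2p̄(1 − p̄)/330)
- SE1 = √(f × [p1(1 − p1) + p2(1 − p2)]/330)
- Probability of a significant result favouring the output = Φ[(s − 1.96 × SE0)/SE1]

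Three values of f are used: 3.7 (the design effect above), 1.0 (no clustering adjustment) and 0.7 = 1 − 0.3 (cases randomized within clinician).

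Worked example, s = 0.05 and f = 0.7: SE0 = 0.0325, SE1 = 0.0325, and (0.05 − 1.96 × 0.0325)/0.0325 = −0.42 (unrounded SEs used), so Φ = 0.336.

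| Assumed shift | f = 3.7 | f = 1.0 | f = 0.7 |
|---|---|---|---|
| 5 points | 0.098 | 0.250 | 0.336 |
| 10 points | 0.267 | 0.734 | 0.871 |

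With no shift, the probability in that direction is 0.025. Control rates of 40% or 55% in place of 50% change these entries by at most about 0.013.

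**4. The exploratory covariate**

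The article does not say what baseline diagnostic uncertainty is. If it is the initial confidence item, covariate and outcome are the same rating in control cases but two different ratings in intervention cases. The adjusted between-arm confidence model could not then be read as adjusting for baseline. If it is something else, such as a chart-based measure, this problem does not arise.

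**The case against.** The strongest reply is that the trial is pragmatic and its primary predictor is access to the output versus no access. Reconsidering a case because an output has arrived is part of what providing the output does, so the contrast is a legitimate total effect. That stands. A reader might infer that the randomized comparison is invalid; the article does not support that. What remains is that the stated objective is efficacy of the output, and the contrast cannot separate its content from the extra look and the repeated question.

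The questionnaire (Multimedia Appendix 1) is not shown, so a closing item for control cases cannot be ruled out. This also stands and limits the point to the procedure as the article describes it.

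A reader might further infer that the adjusted model is wrong as it stands. That depends on what the baseline variable is, which the article does not say, and the model is exploratory.

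Nor does early opening of the link bias the primary model: it has no baseline term and uses the post-output rating. The instruction shows that the risk was seen, but it is a weaker safeguard than a locked page.

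Finally, the shifts in the illustration are invented and upward. Reconsidering an uncertain case could equally lower confidence.

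**Conclusion.** The point holds for the procedure as described. Primary confidence is rated after a further step in intervention cases and, as far as the article shows, with initial impressions in control cases. The primary result should be read as the total effect of access, including reconsideration and repeat rating, and not as the efficacy of the output's content alone.

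The size and direction of the extra component are unknown. The ranges of about 10% to 34% (5-point shift) and 27% to 87% (10-point shift) show sensitivity under stated assumptions; they do not estimate this trial's false-positive rate. The upper ends need an upward shift and the smallest variance factor.

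The weak protection of initial answers matters for the exploratory before-after and adjusted analyses only.

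**What to change.** **If forms can still be changed.** Release the output link inside the online form only after the initial page has been submitted and locked. Add the same closing confidence question to the control form, and compare closing ratings between arms. The cost is a survey setting and one extra item on about 330 control questionnaires. The comparator then includes a brief re-rating, which is a small departure from plain no access. The sample size need not change unless the difference expected against a re-rated control is below 20 points.

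**If data are already collected.** The Results section reports data collection complete as of June 2019, although it also describes enrolment as active. In that case:

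- State that the primary contrast includes reconsideration and repeat rating.
- Compare initial confidence between arms as a check for early viewing of the output.
- Say what baseline diagnostic uncertainty is. If it is the initial confidence item, leave it out of the between-arm confidence model, because in control cases it would be the outcome itself.

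This costs analysis wording and one additional comparison.
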